## Abstract

The use of physiotherapy (PT) in the hospital emergency department (ED) has shown positive results including improvements in patient waiting time, treatment initiation, discharge type, patient outcomes, safety and acceptability of the intervention by medical staffs. These findings originate from studies that primarily focus on musculoskeletal and orthopaedic conditions. Despite a significant number of people visiting the ED, there is a shortage of literature evaluating PT in the ED for elderly populations. The objective of this study is the evaluate the effect of delivering PT in the ED (versus no delivery) in patients aged 75 and over with ‘falls’ complaints. The main objective is the evaluate the effect on the discharge disposition (discharge home, hospitalization). Secondarily, we will evaluate the effect delivering PT on patient-length of stay, the number of falls at 7 days after admission to the ED, changes between the initial and final medical decision regarding patient orientation, and medical staff satisfaction. This study will follow a prospective longitudinal design involving participants aged 75 years and over. We plan to recruit a total n = 336 patients admitted to the ED with a ‘fall’ chief complaint. After consent, participants will be randomized into either the ‘PT-group’ (receiving a prescription and execution of PT within the ED), or to the ‘no-PT group’ (no delivery of PT within the ED). The PT intervention will involve a standardized assessment of motor capacities using validated clinical examinations, and the delivery of rehabilitative exercises based on individual needs. Outcomes will be recorded from the patient’s medical record, and a phone call at 7 days. A questionnaire will be sent to medical staff. The results of this study will help to determine whether PT might be beneficial for the management of this increasing proportion of individuals who come to the ED.

**Trial registration:** (Trial registration number: ClinicalTrials.gov NCT05753319). https://classic.clinicaltrials.gov/ct2/show/NCT05753319.

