There is a shortage of literature evaluating the effects of PT in ED for non-musculoskeletal chief complaints [20]. Data from our hospital [21] and from Gurley et al. [22] reported that ‘falls’ in older populations might account for up to 40% of PT prescriptions [21] or interventions [22] within the ED. Another retrospective study also emphasized the potential for delivering PT in the ED to ‘fallers’ [23]. However, this study did not allow for an estimation of the specific nature of PT service provided (e.g. assessment and/or therapeutic sessions; location within the ED units) or the effects produced on patient discharge and length of stay.

The number of patients aged 75 years and over presenting to the ED increasing, so as their primary complaint identified as ‘fall’ [6,24–26]. It is also estimated that more than 50% of fall patients presenting at the ED report adverse events: recurrent falls, revisits to the ED with subsequent hospitalisations within 6–12 months [27,28], and up to 15% mortality rate one year later [28]. Given the challenges in caring for the elderly population due to frailty and their higher risk for adverse outcomes after an ED visit, there is a need for special attention on screening/assessment and strategies offered to this population in ED [11,29]. To the best of our knowledge, no study has prospectively estimated the effect of delivering PT to patients aged 75 and over admitted in ED with a chief complaint of ‘fall’.

Therefore, the main objective of this study is the evaluate the effect of delivering PT in the ED (versus no PT) in patients aged 75 years and over for ‘falls’ complaints, on the discharge disposition after their ED visit.

The secondary objectives are to evaluate the effect of the intervention (PT vs no PT) on:

the length of stay (LOS) within the ED and the hospitalthe number of falls recorded within the 7 days after admission in EDthe medical staff satisfaction of PT practice in EDthe changes between initial and final EP decision regarding patient orientation (discharge home, acute care unit, hospitalization)

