### Outcomes

All outcomes, measurement time points and aggregations methods are described in Table 2.

**Table 2 pone.0303362.t002:** Summary of outcomes.

Variable	Aggregation method	
	‘PT-group’	‘no PT-group’
Age, at ED admission	mean (SD)	
Gender		
female	n (%)	
male	n (%)	
Emergency Severity Index Level		
1	n (%)	
2	n (%)	
3	n (%	
4	n (%)	
5	n (%)	
Average	mean (SD)	
Primary diagnosis		
Toxicologic	n (%)	
Traumatic	n (%)	
…	n (%)	
Orientation, at discharge from ED (EU patients)		
Return to home	n (%)	
Hospitalization	n (%)	
SSHU	n (%)	
Orientation, at discharge from ED (OU patients)		
Return to home	n (%)	
Hospitalization	n (%)	
Number of falls, within 7 days	n (%)	
Average	mean (SD)	
Number of re-visits to ED for falls, within 7 days	n (%)	
Average	mean (SD)	

Abbreviations: ED: Emergency department; EU: Emergency Unit; OU: Observation Unit; PT: physiotherapy; SD: Standard deviation.

Characteristics of patients at admission to ED will include: gender and age, emergency severity index level, and primary diagnosis.

The primary outcome will be the patient orientation at discharge from the ED according to the defined pathways: return to home (after ERU or SSHU), hospitalization (after ERU or SSHU) or SSHU (after ERU).

The secondary outcomes will be: the length of stay at the ED, or hospital (LOS-ED, LOS-hos) calculated as the duration between admission and discharge from the ED and hospital; the number of re-visits to ED for fall complaints (within 7 days). These outcomes will be found from the medical record of the patient. In addition, a study investigator will call the patient (phone) after 7 days to collect the number of falls since discharge from ED (follow-up).

At the end of the study, the ED medical staff will be asked about their experiences in providing PT within ED: for elderly populations, and in general context. To gather this information, a satisfaction questionnaire containing 4 closed-ended questions, and 2 open-ended questions (for general comments) will be sent electronically via email (Fig 4).

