### Data analysis and interpretation

An independent statistician will perform will perform the analyses (SAS, 9.4^®^).

A review of data will be conducted at the end of the study, prior to statistical analysis. The aim will be to review the progress of the study, potential problems and classify any minor or major deviations. Analyses will be performed in the *Intention-to-Treat* populations corresponding to all randomized patients. A sensitivity analysis will be conducted on the *Per-Protocol* population. This population will include patients without major deviation.

The variables measured at baseline will be described for all patients in both groups by numbers and percentages for each category for categorical variables and the minimum, maximum, average, standard deviation and quartiles for the quantitative variables. (Table 2).

Primary endpoint: the patient orientation at discharge from the ED will be described and compared between the two groups with Chi-square tests, depending on the ED unit of inclusion (emergency unit: 3 modalities: discharge home, hospitalization, observation unit; observation unit: 2 modalities: discharge home, hospitalization).’

Secondary endpoints: LOS-ED and LOS-hos will be described as mean difference and 95% confidence intervals, and compared between the groups using Student’s t tests. The rate of re-visits to ED for fall complaints (characterized as a new episode of fall whose severity requires a re-hospitalization within 7 days) will be compared between groups using Chi-square test. The changes in the patient’s orientation between initial and final decisions will be compared between the groups using Chi-square test. Satisfaction of ED medical staff will be depicted descriptively.

Due to this ‘pragmatic’ approach, it is not possible to compute a priori statistical calculations. The distribution of patients within both units of the ED (EU or UN), the different modalities of patient discharge (Fig 3), and for each group (PT vs no-PT) make it challenging to determine expected differences between groups for the main outcome. As stated, we aim to recruit, as exhaustively as possible, during the inclusion period.

Any missing data will be described and explained. There will be no imputation done on missing data.

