### Issues related to adverse events

A serious adverse event related to this study would be a fall during the delivery of PT. Investigators may report any adverse event (with or without an expected relationship with the intervention) to the study coordinator. If so, a report to the data monitoring committee (DMC) will be made by the investigators. Appropriated care within the ED will be provided in case of adverse event and for post-trial care, if judged necessary. It Is within the scope of the DMC to communicate to relevant parties (e.g., investigators, Ethics committee) if necessary.

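### Falls are defined over 7 days from ED admission but collected only from ED discharge, so falls during the ED stay, when PT is given, do not enter the count

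*Protocol article*

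**What the plan says.** All places are in the protocol article.

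- **Abstract:** the outcome is "the number of falls at 7 days after admission to the ED".
- **Introduction, secondary objectives:** the same origin, "number of falls recorded within the 7 days after admission", listed among the effects of PT versus no PT to be evaluated.
- **Outcomes, text:** "a study investigator will call the patient (phone) after 7 days", and the purpose of the call is "to collect the number of falls since discharge from ED (follow-up". The 7 days are not tied to admission or to discharge. The call is the only source named for the number of falls; the medical record is named for length of stay and ED re-visits.
- **Outcomes, Table 2:** "Number of falls, within 7 days", with no origin.
- **Length of stay:** it is "calculated as the duration between admission and discharge from the ED and hospital", and under Data analysis and interpretation "LOS-ED and LOS-hos will be described as mean difference and 95% confidence intervals", with a t test between arms.
- **Intervention:** the assessment and the daily sessions all take place before the patient leaves the ED.
- **Issues related to adverse events:** "A serious adverse event related to this study would be a fall during the delivery of PT". Investigators may also report any other adverse event, related or not.

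**The concern.** The outcome named in the objective and the outcome collected are different variables. A patient who falls in the Emergency Unit or Observation Unit has an event under the Abstract and the objective, but none under the question asked on the telephone. The collection rule as written therefore cannot deliver the stated objective.

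The missing interval matters because it is when PT patients are mobilised and given gait and balance exercises. Falls at that time are the most direct safety signal for the intervention, and they stay outside the between-arm falls comparison.

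The starting point of the count is also an event after randomisation. The trial compares ED stay between arms, and the Introduction cites evidence that PT in the ED shortens waiting and treatment time. If PT does change ED stay, the two arms are observed over windows that differ in length or in position, depending on when the call is made.

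**Working it through.** The plan has no figure of its own to reproduce here. The check is a comparison of the texts, followed by an illustration.

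**1. Time origin in each place**

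| Place | Start of count | End of count |
|---|---|---|
| Abstract | ED admission | day 7 from admission |
| Secondary objectives | ED admission | day 7 from admission |
| Outcomes, text | ED discharge | call after 7 days, origin not stated |
| Outcomes, Table 2 | not stated | 7 days, origin not stated |

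Nothing in the article reconciles the first two rows with the third. The Outcomes section refers to Table 2 for measurement time points, but the table does not settle the matter.

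**2. Is there another route for in-ED falls?** A fall during PT is reportable as a serious adverse event, and other in-ED falls may be reported in either arm. No section says that these reports are added to the falls count.

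**3. Window if the call is 7 days after admission.** Let L be the ED stay in days. The window is 7 − L. With the same constant fall rate in both arms, the ratio of expected counts (longer-stay arm to shorter-stay arm) is (7 − L_long) / (7 − L_short). The article gives no ED stay in days, so every value of L below is an assumption.

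| L_short vs L_long (days) | Windows (days) | Count ratio with no true effect |
|---|---|---|
| 0.25 vs 0.5 | 6.75 vs 6.5 | 6.5/6.75 = 0.963 |
| 0.5 vs 1 | 6.5 vs 6 | 6/6.5 = 0.923 |
| 0.5 vs 1.5 | 6.5 vs 5.5 | 5.5/6.5 = 0.846 |
| 1 vs 2 | 6 vs 5 | 5/6 = 0.833 |
| 1 vs 3 | 6 vs 4 | 4/6 = 0.667 |

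**4. Window if the call is 7 days after discharge.** The window runs from L to L + 7. Its length is 7 days in both arms, so the ratio from length alone is 1.00. Its position moves with stay: with stays of 0.5 and 1.5 days it covers days 0.5 to 7.5 in one arm and days 1.5 to 8.5 in the other, counted from admission.

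**5. Common to both readings.** The first L days after admission are not observed.

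**6. With one fixed origin and in-ED falls counted.** Both arms are observed for the same 7 days, and the ratio at equal fall rates is 1.00 whatever the stay.

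**The case against.** Several points on the other side are sound.

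- **The call date is open.** A reader might infer that the length of the window necessarily depends on ED stay. The article does not support that. A call 7 days after discharge is a natural reading of a sentence about falls since discharge, and it gives equal lengths. This stands: the length effect is conditional. The conflict of origins and the uncounted ED period remain under either reading.
- **The size may be small.** A reader might put the distortion at one-seventh for a one-day difference in stay. A ratio of 6/7 = 0.86 would need stays of 0 and 1 day. The only ED-stay figure in the article is that 34% of elderly admissions are treated in under 4 hours, and 4 hours is 4/168 = 2.4% of a 7-day window. Nothing in the article supports a full day's difference between arms. On the other hand, daily sessions until discharge show that stays beyond one day are foreseen.
- **Adverse event reporting covers both arms.** A reader might infer that in-ED falls are recorded under PT and lost in the control arm. The article allows any adverse event to be reported in either arm, so that contrast is too strong. The reporting is optional, however, and no section links it to the falls outcome.
- **No test is planned on the fall count.** The analysis section names tests for length of stay, re-visits and orientation changes, but none for the number of falls. No planned test is therefore shown to be biased. The count is still listed as a treatment-effect objective and tabulated by arm.
- **Other sources are not at hand.** The SPIRIT diagram or the full protocol in the supplement may fix the call date. That would settle the window, but it would not remove the conflict within the article.

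**Conclusion.** The point holds as an inconsistency in a secondary outcome that should be corrected. The falls outcome has two conflicting origins, and the collection rule leaves out falls between admission and ED discharge, the period when PT is given. This conclusion needs no assumption about length of stay.

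A distortion of the between-arm count is possible but not established. It needs a difference in ED stay between arms and, for window length, a call timed from admission. Under those conditions and equal fall rates, the assumed stays of 0.5 versus 1 day and 1 versus 2 days give ratios of 0.92 and 0.83; at 0.25 versus 0.5 day the ratio is 0.96. If the call is timed from discharge, only the position of the window shifts, and the article gives no basis for sizing that effect. The primary outcome is not affected.

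**What to change.** Use one fixed origin in both arms, either ED admission as in the objective or randomisation, with the window ending at day 7 from that origin. State it identically in the Abstract, the secondary objectives, the Outcomes text and Table 2.

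Count falls wherever they occur. Take falls in the Emergency Unit, the Observation Unit and on the ward from the medical record in both arms, and the rest from the call. Make the call once the full window has elapsed, and ask about falls up to day 7 from the chosen origin. State that a fall during PT counts in this outcome as well as being reported as an adverse event.

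The cost is a wording change, one line in the call script and one extraction field for in-hospital falls, from a record already used for other outcomes.

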**Fig 4 pone.0303362.g004:**
[figure not shown]
Satisfaction-questionnaire for medical staff.

### Data analysis and interpretation

An independent statistician will perform will perform the analyses (SAS, 9.4^®^).

A review of data will be conducted at the end of the study, prior to statistical analysis. The aim will be to review the progress of the study, potential problems and classify any minor or major deviations. Analyses will be performed in the *Intention-to-Treat* populations corresponding to all randomized patients. A sensitivity analysis will be conducted on the *Per-Protocol* population. This population will include patients without major deviation.

The variables measured at baseline will be described for all patients in both groups by numbers and percentages for each category for categorical variables and the minimum, maximum, average, standard deviation and quartiles for the quantitative variables. (Table 2).

Primary endpoint: the patient orientation at discharge from the ED will be described and compared between the two groups with Chi-square tests, depending on the ED unit of inclusion (emergency unit: 3 modalities: discharge home, hospitalization, observation unit; observation unit: 2 modalities: discharge home, hospitalization).’

Secondary endpoints: LOS-ED and LOS-hos will be described as mean difference and 95% confidence intervals, and compared between the groups using Student’s t tests. The rate of re-visits to ED for fall complaints (characterized as a new episode of fall whose severity requires a re-hospitalization within 7 days) will be compared between groups using Chi-square test. The changes in the patient’s orientation between initial and final decisions will be compared between the groups using Chi-square test. Satisfaction of ED medical staff will be depicted descriptively.

Due to this ‘pragmatic’ approach, it is not possible to compute a priori statistical calculations. The distribution of patients within both units of the ED (EU or UN), the different modalities of patient discharge (Fig 3), and for each group (PT vs no-PT) make it challenging to determine expected differences between groups for the main outcome. As stated, we aim to recruit, as exhaustively as possible, during the inclusion period.

Any missing data will be described and explained. There will be no imputation done on missing data.

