Briefly, patients aged 75 years and over admitted with a chief complaint of a ‘fall’ are first clinically assessed within the EU, to provide a prompt clinical exam, an initial course of action, and an initial decision for orientation. After this first stage, there are three possibilities: (i) the situation is benign and the patient is discharged; (ii) there is a clear indication for hospitalization; or (iii) the clinical situation is unpredictable and the patient can be admitted to the OU for observation/monitoring, treatment, and further assessments. As illustrated in Fig 3, the typical pathway involves patients initially going to the EU where they may be directed to one of the three options: returning home, being hospitalized (in another unit of the hospital), or being transferred to the OU. Once in the OU, these patients may later be directed to either return home or continue hospitalization.

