### Allocation

Participants will be randomly allocated to either study group: PT or no-PT with a ratio 1:1. A SAS program will be used to produce a permuted blocks randomization plan with varying block sizes. This program will be performed by a statistician of the DRI of the University Hospital of Nantes. The randomization will be not stratified.

The investigator can allocate the study group of the included patients using a web browser by connecting to ENNOV Clinical Software: this is a secure, computer-generated, interactive web-response system available at: https://nantes-lrsy.ennov.com/EnnovClinical/login.

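### The planned t test for emergency department length of stay (LOS-ED) ignores unit of inclusion and time before randomisation, so it gives up precision that data already held could recover

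*Protocol article*

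**What the plan says.** All places are in the protocol article.

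- **Test.** Data analysis and interpretation: "LOS-ED and LOS-hos will be described as mean difference and 95% confidence intervals, and compared between the groups using" a two-sample t test (Student's). No split or adjustment is named for these two endpoints.
- **Clock.** Outcomes: both stays are "calculated as the duration between admission and discharge from the ED and hospital". They start at admission, not at randomisation.
- **Order of events.** Study setting: the trial's target patients "are first clinically assessed within the EU, to provide a prompt clinical exam, an initial course of action, and an initial decision for orientation". Abstract: "After consent, participants will be randomized into either" group. Allocation therefore follows arrival and consent.
- **Two units of inclusion.** In Data analysis and interpretation, the primary endpoint is compared "depending on the ED unit of inclusion", with three possible dispositions for EU inclusions and two for OU inclusions. Study setting adds that "the typical pathway involves patients initially going to the EU", from where some are transferred to the OU.
- **Allocation.** "The randomization will be not stratified".

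**The concern.** A patient included in the OU has normally completed an EU stay before being randomised. Those hours cannot be changed by physiotherapy, yet they count in LOS-ED. EU and OU inclusions probably also differ in how long they stay afterwards. The plan recognises this structure for the primary endpoint and drops it for length of stay. An unadjusted t test treats both sources of variation as random error.

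Length of stay is the first secondary objective listed, and the article says that no a priori calculation was possible. No stated power margin is therefore available to absorb avoidable noise. At stake is the width of the LOS-ED interval and the chance of detecting a real shortening, not the validity of the test.

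**Working it through.** **Nothing to reproduce.** The article gives no length-of-stay SD, effect or power. The only planning figure is the recruitment target of 336, which at 1:1 is 168 per arm. Two-sided 5% is assumed, in line with the 95% CI.

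**Formulae.** Let p be the share included in the OU and D the difference between units in mean total LOS-ED.

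- Variance seen by the t test: V = within-unit variance of (pre + post) + p(1 − p)D².
- Variance left after adjusting for unit and pre-randomisation time, if pre and post are independent within unit: A = within-unit variance of post.
- Standard error = √(2 × variance / 168). Gain = A/V.

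**Assumed inputs** (hours, mean (SD), p = 0.5; none is in the article):

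| Set | Pre, EU | Pre, OU | Post, EU | Post, OU |
|---|---|---|---|---|
| 1 | 3 (2) | 12 (6) | 4 (4) | 16 (10) |
| 2 | 2 (1) | 8 (4) | 4 (4) | 12 (10) |
| 3 | 2 (1) | 4 (2) | 5 (5) | 8 (8) |

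**No EU-to-OU transfer**

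- Set 1: within = ½(4 + 16) + ½(36 + 100) = 78; D = 28 − 7 = 21; V = 78 + 0.25 × 441 = 188.25. A = ½(16 + 100) = 58. A/V = 0.31; SE falls from 1.50 h to 0.83 h.
- Set 2: V = 66.5 + 0.25 × 14² = 115.5; A = 58; A/V = 0.50.
- Set 3: V = 47 + 0.25 × 5² = 53.25; A = 44.5; A/V = 0.84.

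Simulation with gamma-distributed times gave 0.31, 0.51 and 0.84. With 25% OU inclusions, set 1 gave 0.28.

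**With EU-to-OU transfer.** The article lists the OU as one disposition of EU inclusions and, in the analysis section, counts both as units of the ED. If LOS-ED includes the OU stay, a transferred EU inclusion adds that stay after randomisation. Let a share q do so.

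- Set 1, added stay 20 (12) h, q = 30%: post variance in EU = 16 + 0.3 × 144 + 0.21 × 400 = 143.2; mean total in EU = 3 + 4 + 6 = 13, so D = 15. V = ½(147.2 + 136) + 0.25 × 225 = 197.85; A = ½(143.2 + 100) = 121.6; A/V = 0.61. SE falls from 1.53 h to 1.20 h.
- Set 1, q = 50%: post variance in EU = 16 + 72 + 100 = 188; D = 28 − 17 = 11. V = 164 + 30.25 = 194.25; A = 144; A/V = 0.74.
- Set 2, added stay 16 (11) h, q = 30%: post variance in EU = 16 + 36.3 + 53.76 = 106.06; D = 20 − 10.8 = 9.2. V = 111.53 + 21.16 = 132.69; A = 103.03; A/V = 0.78.
- Set 2, q = 50%: post variance in EU = 16 + 60.5 + 64 = 140.5; D = 20 − 14 = 6. V = 128.75 + 9 = 137.75; A = 120.25; A/V = 0.87.

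Simulations of these cases gave 0.60-0.76 for set 1 and 0.80-0.89 for set 2.

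**No OU inclusions.** Set 3: A/V = 25/26 = 0.96. Set 1 with 30% transferred: 143.2/147.2 = 0.97. (Set 1 without any transfer would give 16/20 = 0.80.)

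**Power for a 20% shorter post-randomisation stay** (simulated). Set 1 without transfer: 27% to 75%. Set 1 with transfer: 46% to 68% (q = 30%) or 58% to 72% (q = 50%). Set 3: 42% to 50%.

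**Validity.** With no effect, simulated type I error was 0.050 for the t test, with a bias of 0.002 h. With adjustment, the type I error was about 4-6% across simulations, and the mean difference was the same.

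**LOS-hos.** Add to set 1 an inpatient stay for half the patients (the Introduction gives almost 50% hospitalised at this age). Adjustment removes 188.25 − 58 = 130.25 h².

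- Assumed stay 8 (6) days: added variance = 0.5 × 144² + 0.25 × 192² = 19,584 h²; A/V = 1 − 130.25/19,772 = 0.99.
- Assumed stay 5 (4) days: added variance = 0.5 × 96² + 0.25 × 120² = 8,208 h²; A/V = 1 − 130.25/8,396 = 0.98.

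Simulated ratios were 0.98-1.01.

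**The case against.** The strongest reply is that nothing stated is false. Admission to discharge is a usual and sensible definition of length of stay. The t test is unbiased, and covariates for a secondary endpoint are often settled in an analysis plan, which is not shown here. This stands as far as it goes: the clock is not an error, and an unseen plan may already contain the adjustment. But the article does name the test, so the point concerns a stated choice and not a missing detail.

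The second reply is about size, and it largely succeeds. A reader might infer that pre-randomisation time swamps the comparison, or that power would rise from 27% to 75%. That figure needs a large difference between units and no EU inclusion ever moving to the OU, a pathway that the article itself describes. Once transfers are allowed for, the gain shrinks to a moderate one. It is also an inference, not a statement in the article, that OU inclusions have spent part of their OU stay before allocation; the participant flowchart is not shown.

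Third, a reader might extend the point to both stays. The calculation for LOS-hos does not support that. Hours before randomisation are negligible against stays of days, and a difference in hospital stay between units, which could still matter, cannot be quantified from the article.

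**Conclusion.** The point holds for LOS-ED, as an avoidable loss of precision and nothing more. A reader might suspect bias because the outcome starts before randomisation. That does not follow: time before randomisation is balanced between arms in expectation.

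The size is not known from the article. Under the assumptions above, adjustment brings the LOS-ED variance to about 60-90% of its unadjusted value when transfers occur. Since √0.6 = 0.77 and √0.9 = 0.95, the interval narrows by about 5% to 23%. The most favourable case without transfers reaches about 30% of the variance; with no OU inclusions there is hardly any gain. These figures assume that LOS-ED includes OU time and that pre- and post-randomisation times are independent within unit. For LOS-hos, little or no gain is expected. This is a worthwhile, low-cost improvement to a secondary analysis, not a threat to the trial.

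**What to change.** In Data analysis and interpretation, make the main LOS-ED analysis a linear model of the same admission-to-discharge outcome. Include treatment, ED unit of inclusion and time from ED admission to randomisation. Report the adjusted mean difference with a robust 95% CI and keep the t test as a supporting line. Define unit of inclusion as the unit at randomisation, not a unit reached later, so that it cannot be affected by treatment. The same model may be used for LOS-hos for consistency, without promising a gain.

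The cost is one sentence and one derived variable. Admission time is already needed for length of stay, and unit of inclusion for the primary endpoint. The allocation time should be available from the web system, since the article says that its software records users' actions. No new patients or measurements are needed. The small downside is that the main result becomes a model-adjusted mean difference and not a raw one; the quantity being estimated is unchanged.
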